### Criteria for discontinuing or modifying allocated interventions {11b}

Criteria for discontinuing or modifying the allocated intervention for a given trial participant include the presence of a discordant phenotypic-genotypic drug resistance profile that suggests the administration of an ineffective treatment regimen or lack of culture conversion 4 months after initiation of the RR-TB treatment regimen.

### Strategies to improve adherence to interventions {11c}

In line with the design of a pragmatic trial, no strategies are implemented to improve adherence beyond those of routine care to improve adherence to RR-TB treatment. Participants in both trial arms will be phoned to remind them of the date of collection of four study sputum samples.

### Relevant concomitant care permitted or prohibited during the trial {11d}

Trial participation will not require alteration to usual RR-TB care pathways except for the recommendation of the individualized RR-TB treatment regimen in the intervention arm. Any concomitant care interventions are allowed during the trial.

### Provisions for post-trial care {30}

There is no anticipated need for ancillary and post-trial care. The trial is insured for compensation to those who may suffer harm from trial participation.

### Outcomes {12}

The primary effectiveness outcome is the bacteriological response to treatment measured as serial time to liquid culture positivity of sputum samples collected at baseline, weeks 2, 3, 4, 5, 6 and 8 and monthly thereafter. Secondary effectiveness outcomes include cure rate, treatment success rate, relapse rate (recurrence of RR-TB disease) and TB free survival rate in the first 12 months following RR-TB treatment completion. The outcome measure for the feasibility assessment is the number of patients in whom WGS is not successful (due to no *Mtb* growth, culture contamination or failed WGS) and the proportion of participants in whom the treatment recommendation is not followed. For the health economics assessment outcome, unit diagnostic and treatment costs for both arms will be estimated to calculate the total health system cost. The safety outcome is the proportion of participants who experience a serious adverse event.

### Participant timeline {13}

An overview of the screening, enrolment, participant timeline and schedule of assessments is provided in Fig. 2.

**Fig. 2 Fig2:**
[figure not shown]
Schedule of screening, enrolment, interventions, and assessments. *Assessments listed are limited to the study-specific assessments. In addition to these, several assessments are performed on all study participants as per standard of care procedures. W, week; M, month; MGIT, Mycobacteria Growth Incubator Tube. ** Individualization of treatment occurs when drug susceptibility test results become available (whole genome sequencing for the experimental arm; line probe assays and phenotypic drug susceptibility test for standard of care arm). This is expected to occur a median of 5 to 6 weeks after the start of treatment. ***Closeout is performed at month 6 for patients who receive a 6-month treatment regimen

### Sample size {14}

The sample size was simulated for the primary objective using a non-linear mixed effect model. We re-calibrated the model described by Svensson and Karlsson [42] using RR-TB patient data from the Free State province to account for differences in study populations. We hypothesize that the intervention will reduce the mean half-life of mycobacterial load (βexp parameter in the model) by 28%. This would correspond to a difference in median time to culture conversion of 4 weeks (12 vs. 16 weeks). Given the equal balance across arms, and a significance level of 0.05, a total sample size of 173 individuals is needed to achieve 90% power to detect the hypothesized effect size. To account for negative or contaminated cultures at baseline (expected 16%) and death or loss to follow-up prior to achieving culture conversion (expected 21%), the total sample size was set at 248 participants.

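### The enrolment target of 248 does not follow from 173 evaluable participants and the stated losses of 16% and 21%, which in sequence give 261

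*Protocol article*

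**What the plan says.** Everything needed for the check stands in one paragraph of the protocol article, Sample size {14}. The intervention is expected to "reduce the mean half-life of mycobacterial load (βexp parameter in the model) by 28"%. With 1:1 allocation and "a significance level of 0.05", simulation from a recalibrated non-linear mixed-effects model led to the statement that "a total sample size of 173 individuals is needed to achieve 90% power to detect the hypothesized effect size".

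The move from that number to the enrolment target is then explained: "To account for negative or contaminated cultures at baseline (expected 16%) and death or loss to follow-up prior to achieving culture conversion (expected 21"%). On this basis, it says, "the total sample size was set at 248 participants". The paragraph does not say how the two losses were combined, and it mentions no overlap between them.

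Three other places bear on the consequence:

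- The primary analysis row of Table 1 (under Trial design {8}) describes an intention-to-treat analysis that uses all available data.
- Outcomes {12} and Statistical methods {20a} describe serial cultures at baseline, at weeks 2, 3, 4, 5, 6 and 8, and monthly thereafter, analysed in a non-linear mixed-effects model.
- Interim analyses {21b} sets the safety review at half of enrolment, n = 124, which is 248/2.

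**The concern.** A reader given 173, 16%, 21% and 248 should be able to get from the first three figures to the fourth. No correct inflation does so. This is not detail left out of a condensed article, because the article prints all the inputs together with the result, and they conflict.

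At stake is the printed support for the claim that enrolling 248 secures the 90% power attached to 173. The number also fixes the timing of the only planned interim look. If the losses occur as expected, the trial ends with fewer fully evaluable participants than its own calculation asks for.

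**Working it through.** **Inputs** (all from Sample size {14}): n = 173 needed; power 90%; significance level 0.05, sidedness not stated; loss a = 16% (baseline culture negative or contaminated); loss b = 21% (death or loss to follow-up before conversion); target N = 248. The 173 comes from a simulation whose parameters are not printed, so it is taken as given.

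**Step 1: try to reproduce 248.** The correct inflation divides by the fraction retained.

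- In sequence: 173/[(1 − 0.16)(1 − 0.21)] = 173/0.6636 = 260.7, so 261. This is 13 more than 248 (5%).
- Additive, both losses as shares of all enrolled: 173/(1 − 0.37) = 274.6, so 275. This is 27 more (11%).
- One loss only: 173/0.84 = 205.95, so 206; 173/0.79 = 218.99, so 219.

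None gives 248. Incorrect variants that multiply by (1 + loss) come nearer: 173 × 1.16 × 1.21 = 242.8, and (173/0.84) × 1.21 = 249.2. If 205.95 is cut to 205, then 205 × 1.21 = 248.05.

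**Step 2: work back from 248.**

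- Combined loss allowed for: 1 − 173/248 = 30.2%. The stated losses combine to 1 − 0.6636 = 33.6% in sequence, or 37% if added.
- Fully evaluable from 248: 248 × 0.84 × 0.79 = 164.6 in sequence, about 8 short of 173; 248 × 0.63 = 156.2 if added, about 17 short.

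**Step 3: what would make 248 right?**

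- A different second loss: 1 − 173/(248 × 0.84) = 17.0%. Check: 173/0.84/0.83 = 248.1.
- Overlap between the losses, both as shares of all enrolled: 37% − 30.2% = 6.8% of participants. Independence would give 0.16 × 0.21 = 3.4%.
- Partial information: 248 × 0.84 = 208.3 have a usable baseline culture, and 21% of these (43.7) are lost later. To make up 173 − 164.6 = 8.4 participants' worth of information, each would have to contribute on average 8.4/43.7, about 19% of a complete participant.

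The document states none of these.

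**Step 4: approximate power.** Assume a two-sided test and information proportional to the number of participants. Then power = Φ[(1.960 + 1.2816) × √(n/173) − 1.960].

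| Reading | n | Power |
|---|---|---|
| Sequential; those lost contribute nothing | 164.6 | 88.5% |
| Additive; those lost contribute nothing | 156.2 | 86.9% |
| Only the 16% are lost; later losses contribute fully | 208.3 | 94.5% |

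With a one-sided test the three figures are 88.7%, 87.2% and 94.1%, so the unstated sidedness hardly matters.

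**The case against.** The best case for the plan concerns the consequence. The primary model uses every available culture. A participant who dies or is lost before conversion still supplies serial results up to that point, so counting the whole 21% as empty is conservative. Between no contribution and full contribution, power runs from about 88.5% to about 94.5%, and 90% lies inside that range. This stands. A reader might infer from the arithmetic that the trial fails to deliver 90% power or is underpowered, but the documents do not support that.

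The argument does not, however, explain 248. Full contribution from those lost later would call for 206, and the sample size paragraph itself treats the 21% as a loss to be made good, with no intermediate weight stated.

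A second objection is that the additive reading, with 275 enrolled and 87% power, exaggerates the gap. This also stands. Conversion presupposes a positive culture to begin with, so the 21% most naturally applies to those left after the baseline exclusions. The sequential figures are the ones to use, with the additive ones as a remote alternative.

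Third, 1.5 points is small beside the uncertainty of a simulated sample size. The number of runs is not given. If it were 1,000 (an assumption), the Monte Carlo standard error at 90% power would be √(0.9 × 0.1/1000) = 0.95 points, and about 1.3 points at 500 runs. This limits the importance of the shortfall, but it does not reconcile the printed figures.

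Finally, the match at 205 × 1.21 may tempt a reader to conclude that 248 came from dividing for one loss and multiplying for the other. The documents do not show this.

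**Conclusion.** The inconsistency is established. On the natural reading, the stated losses turn 173 into 261, not 248, and 248 enrolled leaves about 165 fully evaluable participants. The connection between 248 enrolled and 90% power is unsupported as printed.

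The effect on power is modest: about 1.5 points below 90% if participants lost before conversion contribute nothing, and possibly none once their cultures are used. These power figures rest on taking 173 as correct, on a two-sided test, on information proportional to the number of participants, and on a normal approximation standing in for the trial's simulation. The enrolment arithmetic needs none of the last three assumptions. Severity is minor to moderate. The design, the analysis and the conduct of the trial are unaffected.

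**What to change.** Keep 248, and with it the interim trigger of 124, and correct the sample size paragraph. It should say that, with the stated losses applied in sequence, 248 enrolled yields about 165 fully evaluable participants and about 88–89% power, and that participants lost before conversion contribute their cultures up to loss.

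If 248 was in fact based on an overlap between the losses, on partial information from those lost, or on a second loss rate nearer 17%, the paragraph should state or correct that input so that 248 yields 173. Such an assumption should be given only if it was the actual basis of the calculation, not chosen now to make the numbers meet.

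The cost is one corrected sentence and a slightly less favourable power figure. No extra participants are needed. Only a wish to keep 90% power on fully evaluable participants under the printed losses would require 261 (275 if the losses add), and that would also move the interim trigger.

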### Recruitment {15}

All newly diagnosed RR-TB patients are notified to the study team either by central data warehouse notification of RIF-resistant cases or through communication by the district MDR-TB team. A district MDR-TB team member briefly informs the patient about the trial. If interested, the patient is referred to a study staff member for informed consent.

## Assignment of interventions: allocation

### Sequence generation {16a}

Randomization 1:1 to the WGS or control arm is automated and performed by Randomizer, a secure dedicated internet site [43].

### Concealment mechanism {16b}

Randomization is web-based and performed in real-time which guarantees unbiased allocation and eliminates the need for a concealment mechanism.

### Implementation {16c}

Randomization is web-based [43]. Minimization is implemented to obtain balanced groups by strata of factors associated with time to culture conversion (baseline mycobacterial load as determined by Xpert Ct value or smear microscopy grading), risk of mortality (age, diabetes, HIV status and if HIV positive whether the viral load is suppressed or not) and history of prior treatment with second-line drugs.

## Assignment of interventions: blinding

### Who will be blinded {17a}?

Participants are blinded to allocation to avoid any influence on adherence or reporting of adverse events by trial arm. Health care providers are not blinded to allocation but are blinded to the routine DST results for patients randomized to the WGS arm (unless required for patient safety) and to WGS results for patients randomized to the control arm.

### Procedure for unblinding if needed {17b}

Because the trial is single-blinded, where only the patient is blinded, we do not anticipate any circumstances under which unblinding is needed during the trial.

## Data collection and management

### Plans for assessment and collection of outcomes {18a}

The date of liquid sputum culture positivity is extracted from the MGIT instrument. Clinical and laboratory patient data is captured from the patient’s medical file, the South African DoH DR-TB treatment paper file and/or the Electronic Drug-Resistant Tuberculosis Register [44] (EDRWeb), and the NHLS laboratory Track Care system. Data extracted include TB treatment history, co-morbidities, HIV-related information, chest X-ray, sputum results (Xpert, LPA, smear microscopy), relevant laboratory test results, audiological screening, electrocardiogram, initial RR-TB regimen and drug doses, regimen adjustments, adherence, concomitant medications, toxicity, and treatment outcomes. The phenotypic drug resistance profile of the participant’s *Mtb* isolate is obtained by standard phenotypic drug resistance tests. The genotypic drug resistance profile is obtained through standard DNA extraction and sequencing procedures. Raw sequencing data will be retrieved from the Illumina Minseq instrument and analysed using the XBS bioinformatics pipeline [41]. Any failures encountered during the laboratory or bioinformatic analytic steps of the determination of the drug resistance profile will be entered in the electronic study database. Information on the prescription of WGS-guided individualized RR-TB treatment regimens will be captured through the secure treatment recommender web app. For the health economics assessment outcome, data on patient socioeconomic status, household assets, illness, and treatment-related costs, is collected by administering a questionnaire (adapted from a validated tool [45]) in the first month, after 6 months, and at the end of treatment for patients receiving more than 6 months of treatment. Data on quality of life is collected monthly using the EQ-5D-5L questionnaire [46]. Serious adverse events (SAEs) data will be captured from the SA DoH Pharmacovigilance form [17] and extracted from EDRWeb [44] and graded by an independent physician.

### Plans to promote participant retention and complete follow-up {18b}

Given the pragmatic design, there are no plans to promote participant retention beyond those implemented by the routine RR-TB care program.

### Data management {19}

Data will directly be entered in the electronic Research Electronic Data Capture (REDCap) database [47], which is developed to ensure data security and promote data quality through real-time data entry validation for data types and range checks. Source data collected as printouts such as pictures of the line probe assays will be captured in pdf format and stored in the REDCap database. Similarly, a picture of the signed informed consent form is uploaded in the electronic database. The REDCap database system employs various methods to protect and secure the data stored in the database.

### Confidentiality {27}

We use REDCap [47] to protect the confidentiality of personal data before, during, and after the trial. REDCap is a secure, web application designed to support data capture for research studies. It includes a full audit trail, user-based privileges, and de-identified data export mechanisms to statistical packages. Access to specific study data in REDCap will be restricted to the relevant members of the study team with authentication through password credentials.

### Plans for collection, laboratory evaluation and storage of biological specimens for genetic or molecular analysis in this trial/future use {33}

Sputum samples will be collected for laboratory evaluation and storage for genetic analyses of *Mycobacterium tuberculosis* in the current trial and for future use in ancillary studies.

## Statistical methods

### Statistical methods for primary and secondary outcomes {20a}

The primary analysis will be an intent-to-treat analysis. A non-linear mixed-effects model that includes a longitudinal representation of mycobacterial load, probability of bacterial presence in a sputum sample, and a time-to-event model to describe the changes in time to culture positivity in liquid media will be used to compare the bacteriological response between the two trial arms [42]. The feasibility of the WGS strategy will be determined based on the proportion of participants in whom WGS is not successful and the proportion of participants in whom the recommended treatment regimen is not prescribed. For the health economic evaluation, the mean incremental costs incurred by patients and the health care system for the WGS versus the control arm will be estimated. For evaluation of safety, we will compare the SAE rate during treatment between the two arms.

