## Introduction

### Background and rationale {6a}

#### Background

The occurrence of 500,000 cases of rifampicin-resistant tuberculosis (RR-TB) annually threatens TB control and global efforts to reach the targets of the World Health Organization (WHO) End TB Strategy [1]. RR-TB treatment is complex, lengthy, often associated with side effects, and costly from the patient, health care provider, and health care system perspective. This results in poor treatment outcomes, high death rates, and continued transmission of drug-resistant TB in the community and health care settings [2].

Great progress in RR-TB management has been made in the past decade. The WHO endorsement of the first-line molecular line probe assays (LPA) in 2008 resulted in rapid diagnosis of resistance to rifampicin (RIF) and isoniazid (INH) in people at high risk of multidrug-resistant TB (MDR-TB) [3]. Endorsement of the Xpert MTB/RIF [4] assay in 2011 and Xpert Ultra assay in 2017 [5] as the initial test for patients presenting with symptoms of TB has revolutionized RR-TB diagnosis and reduced the diagnostic RR-TB gap, from 7% of patients with bacteriologically confirmed TB being tested for RIF resistance in 2012 to 71% in 2020 [1, 6].

The approval of bedaquiline (BDQ) for treatment of RR-TB enabled the replacement of the lengthy (15 to 18 months) treatment with a shorter (9–12 month) all-oral treatment regimen. Since 2019, a 7-drug regimen including BDQ, a fluoroquinolone (FQ), ethionamide (ETO), ethambutol (EMB), high dose INH, pyrazinamide (PZA) and clofazimine (CFZ) is recommended as the regimen of choice for most patients diagnosed with RR-TB [7]. For patients who previously received treatment for RR-TB or in whom FQ resistance is diagnosed, a longer all-oral regimen [BDQ, linezolid (LZD), a FQ, CFZ and/or cycloserine or terizidone (TZD), with or without additional drugs] can be used. In August 2019, pretomanid (Pa) was approved by the United States Food and Drug Administration in combination with BDQ and LZD for patients with FQ resistance who have not been exposed to these drugs [8].

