## Interventions

### Explanation for the choice of comparators {6b}

The comparator is the standard of care RR-TB management as recommended by the South African national DoH guidelines [40]. All participants randomized to the control arm should initiate a short or long injection-free RR-TB treatment regimen upon RR-TB diagnosis. The care provider can individualize the treatment based on first- and second-line LPA and/or phenotypic DST results. Specifically, according to the guidelines, the dose of INH should be lowered to 300 mg daily in patients with INH-susceptible TB. When mutations in both *katG* and *inhA* are present or when FQ resistance is detected, patients should be switched to a long regimen or start the BDQ + LZD + DLM regimen. Patients with resistance to LZD, CFZ and/or BDQ should start a rescue regimen that is recommended by the Provincial Clinical Advisory Committee.

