**Fig. 1 Fig1:**
[figure not shown]
Strategy for whole genome sequencing-guided drug resistance profile determination and automated individualized treatment recommendation

All participants randomized to the intervention arm start a short or long injection-free RR-TB treatment regimen upon RR-TB diagnosis [40]. WGS is performed in real-time on DNA extracted from early positive Mycobacterium Growth Indicator Tube (MGIT) culture isolates of sputum specimens collected before the start of RR-TB treatment. In a sub-group of patients, culture-free WGS directly on DNA extracted from sputum specimens will be performed to evaluate the effect of a shorter turn-around time. An Illumina MiniSeq instrument is used for sequencing and WGS data are analysed using the compleX Bacterial Samples (XBS) bioinformatics pipeline [41]. Based on the WGS-derived drug resistance profile, the treatment recommender ranks all possible drug regimens for an individual patient. Regimens are scored based on the quantitative drug and regimen features including bactericidal and sterilizing activity, propensity to acquire resistance, toxicity, mechanism of action, route of administration, antagonistic and synergistic interactions, and cost. After taking into account clinical data (presence of contraindications, drug toxicity) and health systems data (drug stock out), the highest ranked 4-drug individualized treatment regimen is recommended for 6 months [34]. When healthcare workers question the WGS-guided treatment recommendation, a central clinical committee (CCC) of international experts in RR-TB treatment and clinical microbiology provides evidence-based guidance to the care provider.

To ensure the safety of participants randomized to the intervention, standard-of-care diagnostics are also performed and can be used to guide treatment when WGS results are not available due to poor quality sequencing reads or in case of negative cultures. In addition, phenotypic DST is performed for the drugs included in the WGS-guided individualized treatment regimen to identify possible errors in WGS-based resistance calling.

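### The safety comparison counts SAEs only while each participant is on treatment, and as a proportion this tends to favour the shorter WGS-guided regimen even if the SAE hazards are equal

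*Protocol article*

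**What the plan says.** Two sections of the protocol article define the safety comparison. Outcomes {12} gives the measure: "The safety outcome is the proportion of participants who experience a serious adverse event". It names no window. Statistical methods for primary and secondary outcomes {20a} gives the window: "For evaluation of safety, we will compare the SAE rate during treatment between the two arms". Neither section mentions person-time or a common follow-up period.

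Treatment length is described elsewhere:

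- **WGS arm:** under Intervention description {11a}, "the highest ranked 4-drug individualized treatment regimen is recommended for 6 months".
- **Control arm:** under Explanation for the choice of comparators {6b}, "All participants randomized to the control arm should initiate a short or long injection-free RR-TB treatment regimen upon RR-TB diagnosis".
- **Length of the short regimen:** the Background says that bedaquiline "enabled the replacement of the lengthy (15 to 18 months) treatment with a shorter (9–12 month) all-oral treatment regimen".
- **End of study follow-up:** the legend to Fig. 2 says "Closeout is performed at month 6 for patients who receive a 6-month treatment regimen".
- **Longer treatment is expected for some:** Plans for assessment and collection of outcomes {18a} schedules a further questionnaire "at the end of treatment for patients receiving more than 6 months of treatment".

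The Fig. 2 legend also expects individualization a median of 5 to 6 weeks after treatment starts.

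**The concern.** Read together, these sections let allocation influence how long SAEs are counted. An SAE in month 8 counts for a control participant who is still on treatment. It does not count for a WGS participant whose treatment ended at month 6. A proportion can only grow with the length of the window, so the arm with the shorter window tends to show the lower proportion for that reason alone.

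Two errors are possible. The trial could report a safety advantage that is partly or wholly a product of the window. It could also fail to see a higher SAE hazard under the algorithm-chosen regimens. The data safety monitoring board's primary role is the SAE difference between arms, and the article offers its safety findings to policymakers.

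**Working it through.** The article states no SAE risk, hazard or power for safety, so there is no published figure to reproduce. What follows is an illustration.

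**Inputs from the article**
- 124 per arm (248 in total, 1:1).
- WGS duration: 6 months. If the 6 months run from individualization at about week 5.5, the total is 6 + 5.5/4.345 ≈ 7.27 months.
- Control duration: 9 or 12 months, the two ends of the range given for the short regimen.

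**Assumptions, not in the article**
- 20% of participants have an SAE by 12 months, with the same constant hazard in both arms.
- Two-sided 5% test of two proportions.

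**Step 1: expected proportions.** h = −ln(0.8)/12 = 0.0186 per month and P(T) = 1 − exp(−hT). This gives 10.6% at 6 months, 12.6% at 7.27, 15.4% at 9 and 20.0% at 12.

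**Step 2: apparent effect with no true difference.** The chance of a significant result favouring WGS is Φ(d/SE − 1.96), where d is control minus WGS and SE = √[p₁(1−p₁)/124 + p₂(1−p₂)/124]. The nominal value is 2.5%.

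| WGS v control (months) | Proportions | Risk ratio | d/SE | False benefit |
|---|---|---|---|---|
| 6 v 9 | 10.6% v 15.4% | 0.69 | 1.14 | 21% |
| 6 v 12 | 10.6% v 20.0% | 0.53 | 2.09 | 55% |
| 7.27 v 9 | 12.6% v 15.4% | 0.82 | 0.63 | 9% |
| 7.27 v 12 | 12.6% v 20.0% | 0.63 | 1.58 | 35% |

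**Step 3: harm that would be hidden.** Under constant hazards the proportions are equal when the WGS hazard is T(control)/T(WGS) times the control hazard. That is 9/7.27 = 1.24, 12/7.27 = 1.65, 9/6 = 1.5 or 12/6 = 2.0.

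**Step 4: sensitivity to the assumptions**
- *SAE risk.* With a 12-month risk of 10% or 40%, the risk ratio for 6 v 9–12 months stays within 0.51–0.71.
- *Dilution.* If 16% of the WGS arm (the article's expected share with negative or contaminated baseline cultures) stay on the control duration, the WGS proportion for 6 v 9 is 0.84 × 10.6% + 0.16 × 15.4% = 11.3%, a risk ratio of 0.74 and a false benefit of about 16%. For 6 v 12 it is 12.1%, a risk ratio of 0.60 and about 40%.
- *Early clustering.* With P(T) = 1 − exp[ln(0.8)(T/12)^k], the false-benefit chance for 6 v 9–12 months falls to 13–33% at k = 0.7 and 9–20% at k = 0.5. With 7.27 months in WGS and k = 0.5 it is 5–13%.

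The direction is the same in every case; the size is not.

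**Step 5: the person-time reading.** Under equal constant hazards, simulated events per person-time on treatment gave a median rate ratio of 0.99–1.00 and favoured WGS significantly in 1.5–2.2% of runs, so the artefact goes. With k = 0.5 the average hazard over T months is proportional to T^0.5/T. The rate ratio is then about √(9/6) = 1.22 to √(12/6) = 1.41, against WGS.

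**Step 6: a common window.** Analysing both arms over the same 6 months gives a ratio of 1.00 and 2.5% in favour of WGS.

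**The case against.** The strongest objection is that no single sentence sets up the biased comparison. The analysis section speaks of a rate and the outcomes section of a proportion. If the authors meant events per person-time, constant hazards leave almost no bias. That is correct, but the article also uses the word rate for cure, treatment success and relapse and never mentions person-time, so the proportion is the natural reading. On the other reading the two sections disagree, and early clustering would push the comparison the other way.

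The duration gap is inferred. No arm-level treatment length is stated, and none is given for the current long regimen or for bedaquiline, linezolid and delamanid. The month-6 closeout applies to patients on a 6-month regimen, not to an arm. Failed sequencing, negative cultures and recommendations that are not followed narrow the gap. All of this stands and limits the size. The bias would vanish only if controls too were treated for about as long as the WGS arm, which the 9–12 months given for the short regimen does not suggest.

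Shorter exposure may also be a real advantage of the strategy. That is fair, but the advantage should be measured over a common period. A window that closes with treatment cannot separate fewer SAEs from fewer months of counting.

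A condensed article may leave the estimator to the full analysis plan. Here, however, it does state a measure and a window, and these two conflict with the described regimens.

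**Conclusion.** The point holds in a limited form. As written, a proportion counted over each participant's own treatment tends to favour WGS under equal hazards. On a constant hazard and a 20% 12-month SAE risk, both assumed, the apparent risk ratio is about 0.53–0.82 and the chance of a falsely significant benefit about 9–55%. Early clustering or dilution of the duration gap makes both smaller.

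A reader might infer that the trial is bound to show a spurious safety benefit, or that its safety result says nothing about the strategy. The documents do not support that. The measure is ambiguous, the arm durations are not stated, the SAE risk is unknown, and part of any difference could be a genuine gain from shorter treatment.

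The point should be fixed but does not threaten the trial. Safety appears as an additional secondary outcome in the abstract and among the exploratory objectives, and the primary analysis is unaffected. At the interim look, when half the participants are enrolled, many will still be on treatment and exposure will be more alike. Any bias left there would make the harm stopping rule less sensitive.

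**What to change.** Reconcile the outcomes and statistical methods sections and state one measure and one window:

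1. **Main comparison:** the proportion with at least one SAE, deaths included, from randomization to month 6 in all randomized participants, whatever their treatment length. Analyse time to first SAE over the same window.
2. **Supportive:** SAEs over the whole treatment period by arm, with person-time, so that later control-arm events are not lost.
3. **Month 12:** add this comparison only if SAE capture after the end of treatment is shown to be comparable between arms. The named sources are a pharmacovigilance form and a drug-resistant TB register, and the article does not show that they record off-treatment events equally.

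The first two items are essentially a change of wording, since planned follow-up reaches month 6 for everyone and SAEs are already being extracted. The drawback is that the main window leaves out control SAEs after month 6, which the supportive analysis shows. The month-12 comparison would need extra extraction after closeout for participants on 6-month regimens, at a cost that the article does not allow one to judge.
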